Codesign is a participatory research approach that actively engages users to ensure that intervention designs are meticulously aligned with their specific needs [23]. Through a combination of methodologies, such as focus group interviews, Delphi consultations, and surveys, the codesign process facilitates the involvement of clinicians, patients, and service users [21]. The study materials and delivery strategies developed through the process are perceived as more applicable and acceptable to inclusion health populations [22], thereby enhancing the relevance and effectiveness of interventions. The double diamond model, a design process framework, also places strong emphasis on stakeholder involvement in identifying problems and developing innovative solutions [20]. This model has been successfully used to guide the codesign process for preventive healthcare services tailored to inclusion health populations [22,23]. This study will be guided by the double diamond model to facilitate the collaborative engagement of stakeholders, including inclusion health populations, healthcare professionals, and engineers, in the codesign of a nurse-led, large language model-empowered agent.

The specific research questions of the current study are (i) What are the factors influencing HBV screening and vaccination among inclusion health populations? and (ii) Is a nurse-led, large language model-empowered agent feasible for improving HBV screening and vaccination uptake among inclusion health populations? Accordingly, the objectives of this study are to develop a double-diamond-guided, nurse-led, large language model-empowered agent and to test its feasibility in improving HBV screening and vaccination uptake within these populations. This study will contribute to equitable HBV preventive healthcare access and the micro-elimination of HBV among the most vulnerable cohorts. Furthermore, the codesign methodology will provide guidance for integrating large language models into nurse-led interventions to address healthcare disparities.

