*Qualitative evaluation*. The study will be tested in a randomized controlled pilot study to identify feasibility issues, refine solutions, and explore potential intervention benefits for participants’ HBV screening and vaccination behaviors. The eligible participants are inclusion health individuals who had not undergone HBV screening or vaccination. Based on Whitehead’s recommendations for the required pilot trial sample size [50], 40 participants will be recruited from two university-affiliated hospitals and their community health centers. Participants will be randomly allocated to the control group or intervention group in a 1:1 ratio using a computer-generated block randomization list prepared by an independent statistician. Allocation concealment will be ensured using sequentially numbered, opaque, and sealed envelopes. Two research assistants will enroll participants and reveal the group assignments by opening the envelopes in sequential order. Participants in the control group will receive a standard 15 min oral health education session focusing on HBV prevention, covering the importance of HBV prevention, screening procedures, vaccination schedules, and follow-up care after HBV diagnosis. Participants in the intervention group will be managed using the nurse-led, large language model-empowered agent (Table 1). Individual, in-depth, semi-structured interviews will be conducted at 1 and 6 months with participants in the intervention group. Interviews will specifically focus on exploring the overall user experience, potential technical barriers encountered during interaction with the agent, changes in their knowledge, attitudes, and behaviors related to HBV screening and vaccination, and perceived areas for improvement. Open-ended questions will be asked to encourage discussion, including the following: (i) How do you perceive the program overall? (ii) How do you feel about your interactions with the agent? (iii) What changes in HBV prevention occurred after participation in the program? and (iv) What do you suggest to improve the program? Each interview will be audio-recorded and transcribed verbatim. Thematic analysis will be used to analyze the data. The feedback from inclusion health populations will be used to refine the study. HBV screening and vaccination rates (specifically tracking one-dose, two-dose, and three-dose completion) will be assessed at the six-month follow-up. To ensure consistent data capture across both groups, these outcomes will be verified via electronic medical records. Additionally, secondary feasibility endpoints, including participant recruitment, intervention uptake, and retention rates, will be calculated. Group differences in these outcomes will be evaluated using the Chi-square test.

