## 4. Discussion

To the best of our knowledge, the study is the first to integrate a large language model-empowered agent into nurse-led care to enhance HBV prevention in inclusion health populations. If the study demonstrates feasibility and yields positive outcomes, it will contribute to HBV diagnosis, immunity, and specialist care linkages, thereby advancing HBV micro-elimination in the most vulnerable cohort. It will also establish a codesign framework for developing domain-specific large language models in nursing care, expanding nurses’ roles in promoting preventive health equity for inclusion health populations.

First, this study will enhance HBV screening and vaccination rates, contributing to HBV micro-elimination in inclusion health populations. In 2016, the World Health Organization adopted the goal of eliminating HBV globally by 2030, defined as a 90% reduction in incidence and a 65% reduction in mortality [51]. Studies from Brazil [52], the United States [53], and France [54] have implemented HBV preventive measures among inclusion health populations, including shelter residents, low-income migrants, and female sex workers. However, even with the provision of free on-site screening and vaccinations, the completion rates for HBV screening and three-dose vaccination have consistently remained below 60% [3]. Significant gaps persist in thoroughly addressing and incorporating healthcare access disparities into program designs. Within the current study, the define phase systematically identified 51 factors influencing HBV screening and vaccination among inclusion health populations. These factors are crucial for comprehensively identifying modifiable intervention targets, including health knowledge, health beliefs, and barriers to healthcare access. Additionally, a qualitative study will be undertaken to further explore the specific cultural barriers to HBV screening and vaccination in the Chinese context, thereby informing culturally tailored strategies. By focusing on these key modifiable factors, this study aims to yield a greater intervention effect on HBV screening and vaccination rates in inclusion health populations. This will ultimately contribute to improved HBV diagnosis, immunity, and care linkage, thereby advancing the micro-elimination goal within this vulnerable cohort.

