## 5. Conclusions

Based on the Double Diamond model, this study aims to codesign and test a nurse-led, large language model-empowered agent for HBV prevention among inclusion health populations. It will perform human–agent interactive consultation, intelligent case management, and care coordination, as well as collaborate with a nurse-led multidisciplinary team to manage HBV screening, vaccination, and specialist care linkage. The comprehensiveness of the intervention components is ensured by thoroughly exploring modifiable factors influencing HBV screening and vaccination among inclusion health populations and by identifying effective nurse-led intervention components (e.g., health education, counseling, and case management) targeting these factors. Fine-tuning and retrieval-augmented generation techniques will be employed to enhance the performance of agents for HBV prevention. Importantly, the engagement of diverse stakeholders will be pivotal in identifying and addressing the unique HBV prevention needs of inclusion health populations. This study is anticipated to demonstrate feasibility and have positive impacts on HBV screening and vaccination rates among inclusion health populations. It has the potential to advance HBV micro-elimination among this vulnerable cohort while also providing an innovative codesign framework for integrating large language models into nursing practice to address preventive health disparities.

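### Feasibility is posed as a yes/no question to be tested, but the pilot's feasibility rates are secondary, only calculated, and judged against no pre-set mark

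*Protocol article*

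**What the plan says.** All references are to the protocol article.

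- **Section 2 (Background)** asks as its second research question: "Is a nurse-led, large language model-empowered agent feasible for improving HBV screening and vaccination uptake among inclusion health populations". The matching objective is "to test its feasibility in improving HBV screening and vaccination uptake within these populations".
- **Section 3.5 (Deliver Phase)** describes a 1:1 randomised pilot in which "40 participants will be recruited from two university-affiliated hospitals and their community health centers". Its purpose is "to identify feasibility issues, refine solutions, and explore potential intervention benefits". On feasibility it says that "secondary feasibility endpoints, including participant recruitment, intervention uptake, and retention rates, will be calculated". The sentence that follows assigns group differences to a chi-square test. No target, pass mark, progression rule or precision goal is given for these rates, or for screening and vaccination uptake.
- **Section 4 (Discussion)** attaches the expected contribution to a condition: "If the study demonstrates feasibility and yields positive outcomes".
- **Section 5 (Conclusions)** states: "This study is anticipated to demonstrate feasibility and have positive impacts on HBV screening and vaccination rates among inclusion health populations".

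Numeric criteria appear elsewhere in section 3.4: at least 60% accuracy for choosing the foundation model, and at least 75% agreement for Delphi consensus. Neither concerns the pilot.

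**The concern.** The question and the analysis do not match. A question of the form *is it feasible?* needs a rate and something to hold that rate against. The Deliver Phase supplies rates, ranks them as secondary without naming a primary outcome for the pilot, and states one test, which answers a different question (do the arms differ?).

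For two of the three rates the test has nothing to compare. Recruitment is counted before randomisation, and agent uptake exists only in the intervention arm.

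At stake is the meaning of demonstrating feasibility in the Discussion and Conclusions. If the bar is picked once the rates are known, by a team that already expects a favourable answer, the same data could be reported as feasible or not feasible.

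**Working it through.** **Inputs.** From section 3.5: 40 participants, 1:1, so 20 in the agent arm. The plan states no feasibility rate, so every true rate below is an assumption, as is every bar.

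**The plan's own figure.** The 40 comes from a cited pilot-size recommendation, with no error rate, power, target rate, precision or dropout printed. It cannot be reproduced from the article and is not challenged here.

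**Formula.** The chance that the observed rate meets a bar of k out of n when the true rate is p is the binomial tail P(X ≥ k) = Σ C(n, x) pˣ (1 − p)ⁿ⁻ˣ, summed over x = k to n. Intervals are exact (Clopper-Pearson).

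**Step 1. How far the choice of bar drives the verdict.**

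| Rate | n | Assumed true rate | Bar | Chance of meeting it |
|---|---|---|---|---|
| Agent uptake | 20 | 60% | 50% (10/20) | 0.872 |
| | | | 60% (12/20) | 0.596 |
| | | | 70% (14/20) | 0.250 |
| | | | 80% (16/20) | 0.051 |
| Retention | 40 | 70% | 60% (24/40) | 0.937 |
| | | | 70% (28/40) | 0.577 |
| | | | 80% (32/40) | 0.111 |

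**Step 2. How little one observed rate settles.** An uptake of 15/20 (75%) has an exact 95% interval of 51% to 91%. A retention of 32/40 (80%) has one of 64% to 91%: it meets a bar of 70%, 75% or 80% and misses one of 85% or 90%.

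**Step 3. Whether the chi-square test fills the gap.** It does not, because it contains no standard. Even as a comparison of retention between arms it says little: with 20 per arm and assumed rates of 90% and 80%, its power is about 14%.

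**Step 4. Whether pre-set marks can work at the planned size.** Illustrative marks:

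- Retention, go at 30/40 or more, stop below 24/40. Go probability: 0.035 at a true 60%, 0.970 at a true 85%. At a true 60%, P(X ≤ 23) = 0.432 gives stop, and the remaining 1 − 0.035 − 0.432 = 0.533 gives modify.
- Uptake, go at 14/20 or more, stop below 10/20. Go probability: 0.058 at a true 50%, 0.913 at a true 80%. At a true 50%, P(X ≤ 9) = 0.412 gives stop, and 1 − 0.058 − 0.412 = 0.530 gives modify.

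Both marks seldom pass a poor rate and usually pass a good one with no added participants. A poor rate leads to modify about as often as to stop, so the middle zone needs a stated consequence.

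**The case against.** The strongest reply is that this is an absence, and that a condensed article may leave progression criteria to a full protocol or analysis plan. That stands as far as the numbers go: criteria may exist elsewhere, and the missing figures alone would not be a finding. It does not remove the mismatch in the printed text, where an objective to be tested is served by secondary rates and by a test that cannot answer it. One could also read the chi-square sentence as covering only screening and vaccination rates. In that case the feasibility rates have no stated analysis beyond calculation, and the point is unchanged.

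The second reply is that the pilot is formative: it sits under a qualitative heading, with interviews at 1 and 6 months, and its results feed refinement of the agent. This is right and limits the point. That purpose needs no pass mark.

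Three stronger readings are tempting and are not supported:

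- *The pilot as a whole cannot deliver.* Only the yes/no claim is affected, given the formative purpose above.
- *The large trial depends on this verdict.* The limitations in section 4 call for a large trial because intervention benefits are not robustly assessed here. They do not make it conditional on feasibility. The Discussion's own condition also pairs feasibility with positive outcomes, and the Conclusions merely anticipate it.
- *A pass mark for screening in the agent arm can be taken from the article's 28% and 64%.* The first is past screening among inclusion health populations at large, while the pilot enrols people not yet screened or vaccinated. The second comes from a review that also covered general populations. A single-arm mark would also ignore the randomised control.

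**Conclusion.** The point holds for the feasibility question and the statements built on it, and not for the pilot's formative aim. As written, the plan yields rates with no agreed way to call them adequate, so a claim of demonstrated feasibility would depend on a bar set afterwards. Under an assumed true uptake of 60% in 20 people, that choice moves the chance of success from 87% to 5%. Under an assumed true retention of 70% in 40 people, it moves it from 94% to 11%.

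These sizes rest on assumed true rates and bars, on all 40 being randomised 20 to 20, and on retention being counted over everyone randomised. The sample size is not judged wrong. The change should be made before the pilot starts, but nothing here invalidates the study.

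**What to change.** In section 3.5, keeping 40 participants:

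1. Name recruitment, agent uptake and retention as the pilot's primary outcomes, in line with the objective in section 2.
2. Report each rate with an exact 95% confidence interval in place of the between-group chi-square test.
3. Before the first randomisation, set go / modify / stop marks for retention and agent uptake, and a rule for combining them (for example, go only if both reach go, stop if either falls to stop, otherwise modify). Illustrative marks, for the sponsor to confirm: retention at six months over all randomised, go at 30/40 or more and stop below 24/40; agent uptake, on a definition fixed in advance, go at 14/20 or more and stop below 10/20.
4. State in sections 4 and 5 that demonstrating feasibility means meeting these marks. If criteria already exist in a fuller document, cite them in section 3.5 and align the wording.

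**Cost.** A few sentences in the protocol and the registry record while the Deliver phase is still pending, with no added participants or visits. The real price is that the sponsor commits in advance to a result that could be modify or not feasible.

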## 1. Introduction

“*When the Great Way prevails, the world community is equally shared by all*.”——Confucius

This profound adage from the Analects of Confucius envisions a society in which resources and opportunities are equitably distributed [1]. In this vision, health equity advocates for a fair distribution of health resources and outcomes, ensuring equal opportunities to achieve optimal health outcomes for all [2]. Nonetheless, inequities continue to challenge health outcomes for inclusion health populations, particularly in the efforts to eliminate hepatitis B virus (HBV) due to their insufficient access to preventive health resources, including screening and vaccination services [3].

HBV, a major liver disease etiology, disproportionately affects inclusion health populations, including rural residents, migrant workers, and individuals of low socio-economic status [3]. Their high-risk behaviors, including tattooing, unprotected sex, and blood selling, results in elevated HBV exposure rate ranging from 10.1% to 31.8% [4,5]. The HBV prevalence in these populations, ranging from 4.4% to 39.2% [6], significantly exceeds that in the general population (3.3%) [7]. Nonetheless, a systematic review showed that less than 28% of inclusion health populations undergo HBV screening and fewer than 30% complete a three-dose HBV vaccination regimen [3]. Consequently, approximately 90% of HBV cases remain undiagnosed [8] and 86% of inclusion health populations remain unimmunized [9], perpetuating disease transmission, exacerbating advanced liver diseases, and threatening global targets for eliminating HBV by 2030 [10]. Ensuring equitable access to HBV screening and vaccination services is imperative.

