Inclusion health populations, including rural residents, migrant workers, and individuals of low socioeconomic status, experience a disproportionately high HBV burden. The seroprevalence of HBV infection among rural residents in China [27], Nigeria [28], and Camerron [29] ranged from 6.7% to 10.7%. Migrant workers also face elevated risks, with a high proportion (58.19%) undertaking high-risk behaviors, such as unprotected sexual behavior [30]. Their HBV seroprevalence rates have reached 8.1% in China [31], 11.4% in Thailand [32], and 17.24% in Indonesia [33]. A pooled rate of 21.05% was reported among sanitation workers with low socioeconomic status [34]. Despite this elevated risk, less than 27.5% of these individuals were screened for HBV [3]. For instance, a recent study of 320,000 individuals, including poor people, rural residents, uninsured individuals, and unhoused people, found that only 16.3% had previously screened for HBV [35]. Additionally, the pooled proportions of HBV vaccination (at least one dose) and prior immunization among inclusion health populations were only 37% [3] and 14.2% [9], respectively. Studies also highlighted their low rates of follow-up testing (43%), treatment (15.9%), and specialist care linkage (32%) after HBV diagnosis [3,36]. Consequently, approximately 30% of them had liver cirrhosis at initial disease presentation and experience a high HBV-induced liver disease burden [36]. However, targeted interventions are lacking and should be developed to ensure equitable access to HBV preventive services for inclusion health populations.

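### The pilot's only named between-group analysis is a Chi-square test, which serves its exploratory aim poorly at 20 per arm; risk differences with intervals should lead

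*Protocol article*

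**What the plan says.** Section 3.5 (Deliver Phase, qualitative evaluation) describes a randomized pilot: "40 participants will be recruited from two university-affiliated hospitals and their community health centers". Allocation is equal, which gives 20 per arm. The size rests on a cited rule for pilots: "Based on Whitehead’s recommendations for the required pilot trial sample size".

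The binary outcomes are then listed. "HBV screening and vaccination rates (specifically tracking one-dose, two-dose, and three-dose completion) will be assessed at the six-month follow-up", and "secondary feasibility endpoints, including participant recruitment, intervention uptake, and retention rates, will be calculated". The next sentence fixes the comparison for all of them: "Group differences in these outcomes will be evaluated using the Chi-square test".

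Section 3.5 states no alpha, continuity correction, effect measure or interval for this comparison. It gives the pilot's purpose as finding feasibility problems and looking for possible benefit. The limitations in Section 4 leave effectiveness to a later large trial.

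**The concern.** The method is stated, so this is a question about a choice and not about missing detail. With 20 per arm, a p-value says little about how large a benefit the data allow. A result above 0.05 can easily be taken as absence of benefit, and a result just below it may depend on which form of the test the software applies.

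There are two further points. One-, two- and three-dose completion are cut-points of a single 0-3 count, so testing them one by one means correlated looks at the same outcome. And, read literally, the sentence also tests recruitment and intervention uptake between arms. Recruitment happens before allocation and the control group has no agent, so neither has a between-arm contrast.

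**Working it through.** **Inputs.** N = 40, 1:1 (Section 3.5). This figure cannot be reproduced, because the article gives only the cited rule, with no alpha, power, effect or dropout. Background rates: "less than 28% of inclusion health populations undergo HBV screening and fewer than 30% complete a three-dose HBV vaccination regimen" (Section 1); one study "found that only 16.3% had previously screened for HBV" (Section 2); also in Section 2, 37% with at least one dose and 14.2% previously immunized. Nurse-led effect (Section 1): 64% screened and a 2.61-fold increase in vaccination, not stated to be an odds ratio or a risk ratio.

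**Assumptions.** Two-sided alpha 0.05; complete follow-up; the published rates serve as arm rates. They are not six-month rates in people who had not been screened or vaccinated, so they only mark a range. Retention of 90% vs 80% is invented for illustration.

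**Conversion of 2.61 as an odds ratio.** p2 = 2.61 p1 / (1 - p1 + 2.61 p1).
- From 30%: 0.783 / 1.483 = 52.8%
- From 37%: 0.9657 / 1.5957 = 60.5%
- From 14.2%: 0.3706 / 1.2286 = 30.2%

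As a risk ratio, 30% becomes 78.3% and 14.2% becomes 37.1%.

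**Method.** All 21 x 21 = 441 tables were enumerated and weighted by the product of the two binomial probabilities. The corrected p-value is never below the uncorrected one, so the chance that the two disagree is the difference in their power. The smallest expected count is 20 x min(p, 1 - p), where p is the mean of the two rates. A table has an expected count below 5 when it holds fewer than 10 events or fewer than 10 non-events in total.

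| Scenario | Power, uncorrected | Power, corrected | Disagree | Smallest expected count | Chance of a count below 5 |
|---|---|---|---|---|---|
| Screening 28% vs 64% | 62% | 48% | 14% | 9.2 | 0.1% |
| Screening 16.3% vs 64% | 90% | 81% | 9% | 8.0 | 0.7% |
| Three doses 30% vs 52.8% | 30% | 18% | 12% | 8.3 | 0.8% |
| Three doses 30% vs 78.3% | 88% | 79% | 9% | 9.2 | 0.1% |
| At least one dose 37% vs 60.5% | 29% | 19% | 11% | 9.8 | 0.1% |
| Low rate 14.2% vs 30.2% | 23% | 13% | 10% | 4.4 | 61% |
| Low rate 14.2% vs 37.1% | 39% | 26% | 13% | 5.1 | 40% |
| Retention 90% vs 80% | 14% | 5% | 9% | 3.0 | 93% |

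**Size.** At a common rate, the uncorrected test rejects at most 5.3% of the time (near a rate of 0.31). The corrected test stays near or below 2%.

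**What an interval adds.** For 6/20, the Wilson limits are 14.5% and 51.9%. With 6/20 in both arms, the Newcombe half-width is sqrt((0.300 - 0.145)^2 + (0.519 - 0.300)^2) = 0.268. The result is therefore p = 1.0 with an interval of -27 to +27 points. For 11/20 vs 6/20 the difference is 25 points, the interval -5 to 50 points and the uncorrected p = 0.11.

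**Dependence on the form of the test.** For 13/20 vs 6/20: uncorrected 0.027, corrected 0.057, Fisher 0.056, Boschloo 0.038; risk difference 35 points, interval 4 to 58. Uncorrected Chi-square and Fisher disagree at 0.05 in 28 of the 441 tables, always with Fisher the non-significant one. With the arm sizes as the fixed margin, the unconditional exact tests side with the uncorrected Chi-square in most of those 28: Boschloo in 20, Barnard in 24.

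**The case against.** The strongest reply is that no invalid inference is shown. That stands. A reader might infer that the Chi-square verdict breaks down against exact methods, but the disagreement is mainly with Fisher's conservatism. Unconditional exact tests, and the Newcombe interval for 13/20 vs 6/20, mostly agree with the uncorrected Chi-square. Replacing it with Fisher would be a trade-off and not a correction.

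A reader might also infer that the outcomes are sparse throughout. The article's figures do not support this: in the screening scenarios and at vaccination rates of 30% or more, the smallest expected count is 8 or higher. Sparsity is plausible only for low-rate outcomes and for high retention.

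Nesting does not invalidate a single 2x2 test, and the article does not say that the dose outcomes will go into separate tables. Nor is it right that no effect can be obtained: arm rates will be reported, so a difference can be derived. Intervals and small-cell rules may also stand in an analysis plan that is not shown.

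Finally, the article already presents the pilot as exploratory, admits that its evidence on benefit is weak and urges caution over group differences. It nowhere says that a non-significant result would be read as no benefit. This limits the harm. It does not make a significance test the right leading analysis for such a pilot.

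**Conclusion.** The point holds as a matter of fitness for purpose, not validity. The article names one between-group method, leaves its form open and applies it to every binary outcome in 20 per arm. Under the assumed rates and two-sided 0.05, power is about 62% for 28% vs 64% and 30% for 30% vs 53%. It is higher, at 88% to 90%, only if 2.61 is a risk ratio applied to 30% or if control screening is as low as 16.3%. The unstated continuity correction alone decides significance in about 10% to 14% of pilots in the main scenarios (28% vs 64%, 30% vs 53%, 14.2% vs 30%), and in 9% to 14% across all those tried. A null p-value can sit beside an interval of -27 to +27 points. The weakness is modest, and an analysis plan could add to the method. But the stated sentence does not give what an exploratory pilot most needs, and part of it cannot be carried out as a between-arm comparison.

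**What to change.** Replace the Chi-square sentence in Section 3.5 with text to this effect:

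- For screening, vaccination and retention, report each arm's rate and the risk difference with a 95% interval (Newcombe or Miettinen-Nurminen) as the main result.
- Analyse doses received (0-3) once, as an ordered outcome, with an exact rank-sum test; show the one-, two- and three-dose rates descriptively with their intervals.
- If p-values are kept, name a single test in advance, for example an unconditional exact test such as Boschloo's, and label all of them exploratory.
- Report recruitment, and agent uptake in the intervention arm, descriptively without a between-arm test.

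The cost is a little more analysis text and fewer clear-cut statements of significance. The sample size and data collection do not change.
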